### Concealment mechanism {16b}

Since the allocation sequence is generated using an algorithm, the group assignments are unpredictable and unknown to participants and experimenters until after the script is run. This takes place at least 2 weeks after the Baseline Cognitive Session. The group assignment is done once all participants of the same batch have completed the Baseline Cognitive Session. Prior to that, participants are assigned an enrolment ID that runs chronologically in the sequence of their recruitment. Hence, both experimenters and participants are unaware of participant’s group assignment until the allocation is completed.

### Implementation {16c}

A dedicated smaller team of research personnel is responsible for conducting the Baseline Cognitive Session and running of the group allocation script. This restricts data access to confidential participant data to a selected few within the research team. In addition, as the Baseline Cognitive Session involves mostly standardised tasks, all responsible research personnel are intensively trained in both administration and scoring of the tasks to ensure consistency. Before the allocation process, participants will be assigned a recruitment ID indicating their recruitment batch. Once participants have been assigned to a specific group, a new participant ID that differentiates participant by their group assignment will be provided. Participants will be notified of their group assignment via email or phone and asked to complete an online survey to facilitate scheduling of the remaining sessions.

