### Who will take informed consent? {26a}

Written consents are obtained from participants through two informed consent forms (ICFs) at two different time points. Firstly, a ‘cognitive ICF’ covering all cognitive-behavioural testing and Structure Learning training sessions is signed prior to the first Baseline Cognitive Session. Secondly, an ‘MRI ICF’ covering both the pre- and post-test neuroimaging sessions is signed at the start of the pre-test neuroimaging session.

During the informed consent briefing sessions, trained experimenters introduce participants to the study details and procedures, including the study’s group assignment, participant’s timeline, and payment details. Participants have the opportunity to read through the study information sheet and seek clarifications on any aspects. Written informed consent is obtained from participants once their understanding of the study process is confirmed after all concerns are addressed. In compliance with the Human Biomedical Research Act regulated by the Ministry of Health Singapore, a witness will be present during all briefing sessions to confirm voluntary participation and that participants are not coerced into participating in the study.

The informed consent briefing sessions for both the cognitive ICF and MRI ICF follow a similar structure, with differences in the methods of administration. The cognitive ICF session is conducted remotely using Zoom videoconferencing software, and consent is obtained using Adobe Acrobat e-signature software. The electronic cognitive ICF is sent to the individual participant, experimenter, and witness for sequential signing. The MRI ICF is conducted in-person during the pre-test neuroimaging session. During the MRI consent briefing session, participants receive additional information regarding the risks, potential of incidental findings, and safety considerations related to the MRI scans.

For participants below the age of 21 years, the informed consent process is additionally administered to one of their parents or guardians. A separate remote-guided informed consent briefing session is scheduled before the Baseline Cognitive Session. This session allows parents or guardians to provide consent for their child/ward and to clarify any questions they may have pertaining to experimental procedures that their child/ward will go through.

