## Assignment of interventions: Blinding

### Who will be blinded {17a}

The study adopts a single-blind design with participants blinded to the full details of the Structure Learning training programme under investigation. Participants are informed that they are either in Group A or B without any knowledge of whether that refers to the Training or Control group. Training participants, i.e. participants in Group A, will complete the appropriate Structure Learning stage during each training session without knowledge of the stage progression criterion and the context-target stimuli contingency. Participants are only told to predict the next symbol as accurately as possible based on previously appearing ones. This is especially crucial for the study as it investigates whether cognitive flexibility can be improved via implicit learning from Structure Learning training. Control participants, i.e. participants in Group B, are unaware of the Structure Learning training programme. During the pre- and post-cognitive sessions, the construct measured by each task is non-explicit and never mentioned in the instructions given to the participants (e.g. ‘WCST is a card-sorting task’). This is to prevent task expectations from affecting participants’ performance. The group information is not blinded for experimenters during the administration of tests and data collections. However, manuals to standardise experimenters’ interactions with and instructions to the participants are prepared and intensive training provided for all experimenters to ensure consistency in all administered procedures. Researchers performing the data analysis will not be blinded to the group assignments. However, researchers’ biases are prevented during data analyses by setting hypotheses in advance with sufficient sample size planned prior to data collection. All final analysis scripts will be shared on open science platforms or repositories. Due to ethical regulations, the full data set will not be made available publicly. However, regulated data access can be provided to other researchers under request.

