## Discussion

This paper outlines the protocol for conducting a Structure Learning training programme and the evaluation of its effectiveness with regard to various cognitive domains. Participants are matched based on age, sex, intelligence, and cognitive performances in a Baseline Cognitive Session and assigned equally into either a Control or Training group. Both groups will then be required to complete a pre-training cognitive assessment that comprises of standardised tests that measure intelligence, and language and numeracy skills. Following that, participants undergo the pre-training MRI scans. During a period of 2 weeks, the Training group commences on their Structure Learning training sessions, whereas the Control group will not be given any form of training. Post-training MRI scans will be taken immediately after the end of the 2-week gap. Finally, two post-training cognitive sessions will be conducted for both groups of participants.

As this study is conducted in a single-blind manner, participants are not privy to the group they are assigned to, while experimenters are aware of the group participants are in. This may result in an increased likelihood of experimenter bias, where the experimenter may unknowingly provide certain cues or lead participants in a certain way during Structure Learning training sessions or cognitive sessions. Additionally, there are certain cognitive assessment that requires a slightly level of subjective judgement in scoring participant responses; preconceived notion about the group assigned to the participant may cause experimenters to have slight differences when scoring these responses.

The Structure Learning training outlined in this study is designed to target improvements in CF, as well as potential transfers to other cognitive functions. As highlighted earlier in this paper, cognitive flexibility is an important cognitive function, contributing to better adaptability in dynamic changes in environment [70] and other important activities of daily living. The development of a training will be critical with higher attentions to improve cognitive capabilities across the ages. Additionally, the correlating of behavioural training outcomes to neurological model can also contribute to better understanding of neuropsychological model of learning. This paper will also serve as a basis of reference to assist other researchers in designing their study.

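### The stated participant blinding cannot stand beside the protocol's own account of consent and burden, and group-coded IDs and unmasked analysts leave an avoidable route for bias

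*Protocol article*

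**What the plan says.** **Participants.** Who will be blinded {17a} calls the study single-blind. Participants are told only that they are in Group A or B, "without any knowledge of whether that refers to the Training or Control group". It adds: "Control participants, i.e. participants in Group B, are unaware of the Structure Learning training programme". The Discussion repeats that participants do not know their group.

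**Consent.** Who will take informed consent? {26a} describes a cognitive consent form "covering all cognitive-behavioural testing and Structure Learning training sessions is signed prior to the first Baseline Cognitive Session". The briefing that goes with it includes the group assignment, the participant's timeline and payment.

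**Staff.** The Blinding section says of those who run the tests: "The group information is not blinded for experimenters during the administration of tests and data collections". Implementation {16c} states that once a participant is allocated, "a new participant ID that differentiates participant by their group assignment will be provided". The Discussion accepts that some assessments need judgement in scoring and that a "preconceived notion about the group assigned to the participant may cause experimenters to have slight differences when scoring these responses".

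**Analysts.** "Researchers performing the data analysis will not be blinded to the group assignments". The safeguard offered is that their "biases are prevented during data analyses by setting hypotheses in advance with sufficient sample size planned prior to data collection".

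**The concern.** Two separate matters are at stake.

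The first is a blinding property that is claimed but that the design does not have. The comparator is passive, and most primary outcomes are measured only at post-test. If participants know whether they were trained, expectancy is part of the Training versus Control contrast, and for most tasks no earlier measurement on the same task exists against which to see it. A reader who accepts the single-blind label would believe that expectancy had been controlled.

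The second is a bias route on the staff side that could be closed cheaply. Data are linked through the participant's ID. An ID that shows the group carries that information to whoever scores a sheet or cleans a file under it, including people with no other reason to know it. The protocol concedes the mechanism for subjective scoring. For analysis, it says that bias is prevented by two measures that do not address the choices an analyst makes once the data are open.

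**Working it through.** There is no stated figure to reproduce. The check sets the sections side by side.

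**1. Can a participant be unaware of the training, or of being in it?**
- *Timing.* The cognitive consent form is signed before the first baseline session (Who will take informed consent? {26a}). Allocation is run only after a whole batch has finished that session (Sequence generation {16a}; Concealment mechanism {16b}). So both groups sign the same form, and by the protocol's description it covers the training sessions.
- *Content.* The briefing includes the group assignment. A full study timeline is given at the consent session (Strategies to improve adherence {11c}). The maximum time commitment is disclosed so that people can commit whichever group they enter (Plans to promote participant retention {18b}).
- *Divergence.* Training means 1 h daily for at least 13 days (Strategies to improve adherence {11c}). The total burden is 32 h in Training and 12 h in Control (Participant timeline {13}), a difference of 32 − 12 = 20 h.

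Someone who consented to a study with training sessions and a known maximum commitment, and who then has either daily sessions or none, can tell which group they are in. The A/B label does not hide it. The two statements in the Blinding section therefore conflict with the sections above.

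**2. What masking remains?** The Blinding section separately says that trainees do not know the context-target contingency or the stage progression criterion, and that no participant is told which construct a test measures. Nothing elsewhere contradicts this.

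**3. Where can knowledge of the group affect scoring?** Plans for assessment {18a} lists the non-computerised tasks: WASI Vocabulary, WASI Block Design, the WJIV tasks, verbal fluency and backwards digit span. By Outcomes {12}, the WASI and WJIV tasks are given only at pre-test. Two post-test outcomes remain: backwards digit span, one of three tasks for working memory (a primary construct), and verbal fluency (secondary). No cognitive flexibility task is on the list.

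**4. Do advance hypotheses and a planned sample size prevent analyst bias?** Evaluation of efficacy of Structure Learning training leaves open whether measures are standardised or normalised, whether norms come from published data or the concurrent study, and where parametric tests are possible. Primary outcomes {12} allows both conventional and model-derived measures. A fixed hypothesis and a fixed n settle none of these. Masking the group code while they are settled would.

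**5. Scale, for illustration only.** The documents give no size for any bias. Take n = 50 per group and α = 0.05 from Sample size {14}, and assume a two-sided normal test, no true effect, and a systematic shift of b SD that happens to favour Training. Then SE = √(2/50) = 0.2 SD, and the error rate is [1 − Φ(1.96 − b/0.2)] + Φ(−1.96 − b/0.2).

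| Assumed b (SD) | Favours Training | Favours Control | Total |
|---|---|---|---|
| 0 | 2.5% | 2.5% | 5.0% |
| 0.1 | 7.2% | 0.7% | 7.9% |
| 0.2 | 16.9% | 0.2% | 17.0% |

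A shift the other way would mirror the two middle columns.

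**The case against.** The strongest reply is that most of this is disclosed or mitigated. The Blinding section states openly that experimenters and analysts know the group, and the Discussion lists experimenter bias as a limitation. Manuals, scripted instructions, training, observed first sessions and mostly computerised tasks all limit scoring bias. The passive control is justified in the text and the study is described as close to a pilot. Masking procedures for analysis often sit in an analysis plan, which is not shown here. All of this stands. It narrows the scoring issue to two tasks, but disclosing a bias does not remove it. The two participant-blinding statements and the claim of prevention are wrong as written, whatever another document adds.

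Several stronger readings are tempting and should be resisted:
- *That no blinding exists at all.* Masking of the contingency, the progression criterion and the test constructs survives.
- *That the consent form itself contradicts the protocol.* The form is not shown. The conflict is with the protocol's description of it.
- *That the ID is what unblinds the experimenters.* They know the group anyway, and one experimenter follows each trainee through training. Neutral IDs help only those who later score or process data. No section says that the ID is printed on response sheets.
- *That the bias is known to favour Training.* A superiority aim, a passive control and unmasked staff make that plausible, but the Discussion states no direction and speaks only of slight differences.
- *That an assumed shift can be given as a share of the planned d = 0.25.* That d is for a Group × Time interaction in a pre/post design, whereas most primary outcomes are compared at post-test only. The two are not on the same footing.
- *That the concomitant-care section claims unqualified attribution of effects to training.* Its remark explains why participants should avoid other intervention studies. It is not a claim about blinding.

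**Conclusion.** The point holds in two parts. First, the statements that participants cannot tell Training from Control, and that Controls are unaware of the programme, cannot be reconciled with pre-allocation consent to the training sessions and a later difference of at least 13 daily sessions and 20 h. This rests on the protocol's account of consent and on the ordinary inference that people notice whether they are being trained. Awareness of that kind is largely inherent to a passive control, so the error lies in the claim; it is not something the design could easily have avoided.

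Second, group-coded IDs and unmasked analysts leave a route for bias that could be closed, and the statement that analyst bias is prevented is not supported. Its size and direction are unknown. The error rates of 7.9% and 17.0% are conditional on assumed shifts of 0.1 and 0.2 SD and are not estimates. Manual scoring bears on backwards digit span and verbal fluency only, and not on the cognitive flexibility tasks of the primary aim. Participant expectancy and analysis choices bear on the between-group outcomes more widely.

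**What to change.** 1. Restate the blinding: participants are aware of whether they receive training, and are masked to the contingency, the progression rule and the constructs tested. Limit the conclusion to training versus no training, with expectancy not controlled.
2. Relabel data files and response sheets with IDs that carry no group information. The existing small team that runs the allocation script can hold the key.
3. Have existing staff who neither tested nor trained that participant score the recorded backwards digit span and verbal fluency responses under the neutral ID. This assumes that the records hold the responses and not only a total.
4. Run cleaning, exclusions and composite construction for the between-group outcomes on masked group codes until the scripts are frozen. Keep these files apart from the Structure Learning data, which exist only for Training and would reveal the group.
5. Say that analyst bias is reduced, not prevented.

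The cost is text edits and a modest amount of relabelling and file handling, with care over ID linkage. No new arm or additional staff are needed. Collection was projected to end in June 2023, one month after the protocol version of 11 May 2023, so changes during testing would reach few participants. All five steps can still be taken after collection.

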## Assignment of interventions: Blinding

### Who will be blinded {17a}

The study adopts a single-blind design with participants blinded to the full details of the Structure Learning training programme under investigation. Participants are informed that they are either in Group A or B without any knowledge of whether that refers to the Training or Control group. Training participants, i.e. participants in Group A, will complete the appropriate Structure Learning stage during each training session without knowledge of the stage progression criterion and the context-target stimuli contingency. Participants are only told to predict the next symbol as accurately as possible based on previously appearing ones. This is especially crucial for the study as it investigates whether cognitive flexibility can be improved via implicit learning from Structure Learning training. Control participants, i.e. participants in Group B, are unaware of the Structure Learning training programme. During the pre- and post-cognitive sessions, the construct measured by each task is non-explicit and never mentioned in the instructions given to the participants (e.g. ‘WCST is a card-sorting task’). This is to prevent task expectations from affecting participants’ performance. The group information is not blinded for experimenters during the administration of tests and data collections. However, manuals to standardise experimenters’ interactions with and instructions to the participants are prepared and intensive training provided for all experimenters to ensure consistency in all administered procedures. Researchers performing the data analysis will not be blinded to the group assignments. However, researchers’ biases are prevented during data analyses by setting hypotheses in advance with sufficient sample size planned prior to data collection. All final analysis scripts will be shared on open science platforms or repositories. Due to ethical regulations, the full data set will not be made available publicly. However, regulated data access can be provided to other researchers under request.

### Procedure for unblinding if needed {17b}

Upon completion of the study, participants will be debriefed via email. This debriefing will inform them about their group assignment, i.e. Training or Control in the study. Additionally, participants will be informed of the purpose of the Structure Learning training programme as well as the cognitive tasks that were conducted during the study.

## Data collection and management

### Plans for assessment and collection of outcomes {18a}

Prior to data collection, all experimenters received training to provide standardised instructions and to follow the standard operating protocol (SOP) when administering the tasks. The training sessions spanned 12 h across 4 to 5 days to cover a brief background of the study, SOPs for all tasks in cognitive sessions and Structure Learning training session, as well as safety precautions and preparation work for MRI sessions. During the training, experimenters also had the chance to try out each task and practice giving instructions to their partners (other experimenters undergoing training). Manuals containing SOP for each task were available to experimenters in Teams online and printed out to be used during cognitive sessions. The manual contains the exact instructions that experimenters have to read out, with points to be emphasised bolded in text, as well as other set ups to be standardised (e.g. volume of instructions to be played for CANTAB tasks, baseline and ceiling scoring). This allows experimenters to familiarise themselves with task administration, and to give consistent instructions to all participants. After the training session, newly recruited experimenters will be observed by a full-time research staff during their first cognitive, training, and MRI sessions with participants to ensure that the protocol is executed correctly and to provide any additional feedback. Most cognitive tasks are computerised to improve protocol adherence, with the exception of WASI Vocabulary, WASI Block Design, WJIV tasks, verbal fluency task, and BDS. This also reduces the need for manual data entry so that there would be less errors.

Standardised tests used to measure intelligence (RAPM, WASI Vocabulary, WASI Block Design), language, and numeracy skills (WJIV tasks) are widely validated. The RAPM administered in pre-test and post-test are parallel versions that contain items from Set I and Set II of RAPM [56]. The pre-test and post-test versions have Cronbach’s *a*= 0.59 and 0.64 respectively [57]. No concurrent validity was reported during the construction of Zaaiman et al.’s [57] version of RAPM, but items in both versions were selected using empirical data. Only the vocabulary and block design subtests of WASI-II are administered to measure verbal and non-verbal intelligence respectively. Both subtests have excellent internal reliabilities and high concurrent validity, with Cronbach’s *a*ranging from 0.90 to 0.92 and correlation with other intelligence tests ranging from 0.71 to 0.92 [58]. Lastly, the WJIV tasks also exhibit reliability coefficients ranging from 0.74 to 0.97 and have strong concurrent validity with other tests [59].

Preprocessing will first be performed on rs-fMRI data to enhance quality of data. A standard SPM pipeline (http://www.fil.ion.ucl.ac.uk/spm/software/spm12/, SPM12 v7771) will be employed to model fMRI data. We will reslice the aligned EPI data to 2 × 2 × 4 mm^3^ resolution and apply spatial smoothing with a 6-mm isotropic FWHM Gaussian kernel (SPM smooth). The rs-fMRI noises will be processed by standard denoising pipeline in CONN (https://web.conn-toolbox.org, CONN 21a), including linear detrending, 12 potential motion related noise components, noise components from cerebral white matter and cerebrospinal areas, wavelet despiking. Note that the global signal will not be added as a nuisance regressor as suggested by Murphy and Fox [60]. We also correct for inhomogeneity of the magnetic field by acquiring opposite phase encoded field maps (phase encoded direction A-P and P-A). FSL (version 6.0, using topup function) will be used to preprocess the field maps.

Similarly, processing steps will be conducted concurrently with data analysis of MPM to promote data quality in MATLAB 2020b using hMRI (https://hmri-group.github.io/hMRI-toolbox/). In brief, regression of the log signal from the echoes of all weighted volumes will be used to calculate a map of R_2_* using the ordinary least squares ESTATICS approach [61]. Then the set of 8 echoes for each acquired weighting will be averaged to increase the signal-to-noise ratio. Quantitative R1 maps will first be estimated based on the Ernst Eq [62]. and then further corrected for transmit field inhomogeneities and imperfect RF spoiling [63]. The effective transverse relaxation rate (R_2_^∗^) will be estimated from the logarithm of the signal intensities (from the 8 PDw multi-echo images) at different echo times using a linear regression. Effective PD maps will be estimated from the signal amplitude maps by adjusting for global and local receive sensitivity differences using UNICORT post-processing approach [49]. As the global mean PD cannot be estimated accurately with this post-processing approach, we will scale PD value to 69% of mean white matter. Finally, the MT map will be constructed using the procedure described by Helms, Dathe, and Dechent [64]. After the MPM map are created, segmentation will be performed (grey matter, white matter, and cerebrospinal fluid) combining information from MT and R1 maps. Next, we will perform normalisation by aligning all images to the MNI space in preparation for group analyses. DARTEL (SPM12) will also be implemented to improve alignment across subjects / sessions when normalising to MNI space. Finally, we will apply tissue-specific smoothing on the segmented four MPM maps using voxel-based quantification (VBQ) smoothing with 6-mm FWHM. Smoothing is performed to improve the alignment across participants and boost the signal-to-noise ratio (SNR) for group analyses. MPM values extracted are all based on the smoothed and segmented MPM map.

The MRS data will also be preprocessed using Osprey [65] with MATLAB 2020b. The 128 edit-on and 128 edit-off data will be corrected for eddy-current correction, frequency-and-phase correction, and Fourier transformed prior to grouping on and off spectra and taking the corresponding edit-on and -off spectra differences.

